### Measures: study acceptability and feasibility

Acceptability (e.g. the extent to which clients receiving the intervention consider it to be appropriate, based on anticipated or experienced cognitive/emotional responses [23]) will be assessed in the following ways. In post-intervention exit interviews (~ 60 min in length), clients will be asked the degree to which they enjoyed participating in the intervention, and why. Clients will also be asked about perceived effectiveness (e.g. How effective do you think the intervention was at improving your knowledge of HIV and HIV testing frequency?) and self-efficacy (e.g. How confident are you that you will be able to continue testing for HIV every 3 months?). Additionally, during the final survey, we will ask participants if and how they benefitted from the intervention and what they could be improved. Finally, intervention will be defined as acceptable if > 50% of potentially eligible participants chose to participate. Feasibility (e.g. the belief that the new behavior is concrete and achievable [24]) will be assessed in the following ways: recruitment rate (number recruited per month compared to number expected to be recruited per month from clinic data), as well as refusal and retention rates (screener, randomization, surveys, and intervention from staff reports). We will assess the feasibility and suitability of eligibility criteria (e.g. whether the criteria are clear and sufficient or too restrictive) by examining the proportion of potential participants who are screened as ineligible and the reasons for ineligibility. We will also consider the feasibility and suitability of the data collection assessments (extent of missing or unusable survey data) and the amount of data collection (time taken to complete surveys from study staff). We will collect sociodemographic characteristics at screening and conduct chi-square or t-tests comparing participants and non-participants. We will supplement refusal and retention quantitative data by asking participants who refuse to participate or who do not complete the intervention about why they chose not to participate in exit interviews. We will transcribe and analyze client exit interviews and reasons for non-participation to further document barriers to acceptability and feasibility.

### Measures: health outcomes

Enrolled participants respond to a baseline assessment after they have completed screening and consent. The MOTIVES HIV tester reads the baseline survey to participants to guarantee understanding by clients across a range of literacy levels. Together the screening and consent processes take approximately 15 min to complete; the baseline survey takes approximately 30 min. Participants will complete a shortened six-month survey via response to a link sent to them on their phone. If participants cannot complete the six-month survey on their own, the Study Coordinator will offer to meet them at a local library of their choice and provide a tablet to complete the survey. However, we expect this circumstance be the exception rather than the rule. Participants will receive a $15 gift certificate via text after completing the six-month survey.

The 12-month follow-up survey will have fewer questions and will be completed after the intervention is over, Thus, completing the questions at a *Bienestar* testing location will not confound the outcome of interest. Participants will receive a $15 gift card for participating in the final survey. For those who do not complete their HIV test for that period, we will send a text message reminder to complete the final survey at *Bienestar*. Table 1 describes when each set of questions will be asked.

**Table 1 Tab1:** Health outcomes and measures of interest

Outcome	Instrument	Data collection timepoint
Primary Outcome		
HIV knowledge	Carey MP, et al. Development and psychometric evaluation of the brief HIV knowledge questionnaire (hiv-kq-18). AIDS Education and Prevention. 2002; 14: 174-184.	enrollment, 6 & 12 months
HIV testing behaviors	Extracted from *Bienestar* clinic data	
Secondary Outcomes		
HIV infection	Oraquick/Orasure	enrollment, 3, 6, 9 and 12 months
Covariates of Interest		
Socio-demographic information	Based on previous *Bienestar* questionnaire	enrollment & 12 months
Acculturation	Marín, G et al. Development of a short acculturation scale for Hispanics. Hispanic Journal of Behavioral Sciences. 1987; 9:183–205.	
Mental health	Kessler, RC et al. Short screening scales to monitor population prevalences and trends in non-specific psychological distress. Psychological Medicine. 2002; 32: 959-956.	
Substance abuse	Carballo-Diéguez, A et al. Microbicide Safety and Acceptability in Young Men: Baseline Behavioral Questionnaire. 2010.	
Behavioral Economics	Linnemayr et al. Behavioral Economics and Health. 2017

**Fig. 1 Fig1:**
[figure not shown]
SPIRIT figure

### Data safeguarding and monitoring plan

No drugs will be administered during this study; therefore, the data safeguarding and monitoring plan focuses primarily on confidentiality. We will take the following steps to reduce the risk of disclosure: (1) all study staff will sign a confidentiality agreement requiring them to keep the information obtained in this study private and, if a breach of confidentiality occurs, to report this to the PI within 24 h of discovery; (2) all data will be collected using coded ID numbers; (3) all hard copy materials will be stored in a locked file cabinet/drawer; and (4) only aggregate data that cannot be used to identify individuals will be included in any reports released to other agencies or for publication.

Participants may experience psychological distress or social risks if information that is perceived to be sensitive (e.g. sexual orientation, gender identity, substance abuse, mental health status) is disclosed. Disclosing information about use of illicit drugs may pose legal risks for participants. If a participant exhibits signs of distress, the PI and site coordinator are contacted to ensure that immediate support is provided.

Study staff will be required to report adverse events (AE) or serious adverse events (SAE) to the research team, who will transmit them to the PI immediately. In turn, RAND’s Human Subjects Protection Committee requires the PI to report any AE or SAE within 24 h and will review such events promptly. All the relevant information may not be available at that point. RAND’s Human Subjects Protection Committee will help to determine how serious the event is, what additional information (if any) is needed, and what mitigation procedures should be taken. For example, a misrouting of confidential information from a *Bienestar* staff member to a RAND team member by email instead of a secure file transfer protocol is not a SAE, but quick action to contain the spread of information and delete it correctly can mitigate the potential damage, and some procedural changes and retraining may be needed.

### Data analysis

As previously stated, the primary goal of the analysis is to estimate the intervention’s acceptance and feasibility by determining enrollment and retention rates in the study, using the number of clients screening positive for eligibility, the number of clients enrolling in the study per month, percentage of enrolled clients who respond to the weekly quizzes and are eligible to participate in the testing-based prize drawings, and participants retained in the study. To assess participants’ acceptance of the intervention, we will also ask them to rate their program experience. Semi-structured exit interviews after the study is completed will also provide valuable feedback about the acceptability of the program to clients and the feasibility of the intervention procedures as viewed by clinic personnel.

We will conduct interim data checks to ensure that certain individuals (e.g. either high or low income) are not systematically declining participation in the study. Data checks will be supplemented with bi-weekly team calls in which we review recruitment and retention goals, address issues that arise in the field, and refine our strategy for moving forward. Because most of the study data are uploaded electronically, we avoid issues of double data entry. Interim data checks help ensure the accuracy of data provided.

Blinding participants and staff to the study design raises several issues. Participants will know if they are in the intervention (Information plus group) versus control (Information only group) as the former will be receiving weekly quiz options. However, with the exception of the site PI and the research analyst at RAND responsible for sending all text messages, study staff will be blinded to the data identifiers. All data for subsequent analysis will be de-identified and only the PI and Co-Investigators will have access to the study data. Data will only be unblinded in the case of an AE or SAE, for which the RAND PI needs immediate access to all information to ensure participant safety.

We will conduct group comparisons at six-month intervals to assess the intervention’s short- and mid-term effects. In addition to simple group comparisons at each time point, we will exploit the longitudinal nature of the data by using repeated-measures and time-series techniques. This approach will allow us to examine whether self-reported sexual behaviors persist or decline similarly between the two groups. Repeated measures models will be fitted using Xtreg in the software package Stata. We will use an Analysis of Covariance (ANCOVA) framework to test for group differences, controlling for relevant client characteristics that are found to differentiate the groups at baseline in order to improve the precision that would result from a simple Analysis of Variance (ANOVA) on randomly assigned individuals. For analyses with the dichotomous variables such as HIV testing within a three-months period, we will use a non-parametric McNemar’s test and an analogous multiple logistic regression to control for covariates to assess group differences.

As with any randomized trial (that eliminates selection bias), the first and most direct way to evaluate the impact of an intervention is a simple comparison *D* of the group means in adherence levels.$$ D=E\left[{Y}_i^T\left|T\right.\right]-E\left[{Y}_i^C\left|C\right.\right] $$, *E[Y]* indicates the expected outcome in intervention group *T* and control group *C*.Taking into account the longitudinal nature of the data, this can be written as: $$ D=E\left[\Delta {Y}_i^T\left|T\right.\right]-E\left[\Delta {Y}_i^C\left|C\right.\right] $$In small samples efficiency can be improved by controlling for differences in control variables between the groups that may arise due to chance as discussed above. The approach can be implemented in a regression framework (and again, can be implemented in differences rather than levels): *Y*_*i*_ = *α* + *βT* + *δX*_*i*_ + *ε*_*i*_

As summarized in Table 1, we will explore a range of variables. The independent variables include control variables not only to improve efficiency, but also to learn about the paths through which the intervention works and to identify subgroups that are likely to particularly benefit from the intervention. Furthermore, potential mediators of behavior, such as level of acculturation, may result in improved provider communication and hence information access. For example, some people may want to avoid being seen at a clinic or HIV testing site, but for people who can communicate with providers more easily, this cost is close to zero, and their behavior may not be altered through the intervention. We can test this effect by forming an interaction between the acculturation measure and the intervention. With respect to the dependent variables, the primary outcomes include HIV knowledge and frequency of HIV testing; the secondary outcomes include HIV infection. Continuous variables will be assessed for normality and transformed if needed. Analyses will be conducted for the whole sample as well as for Latino/a MSM and TGW separately to arrive at the potentially differential impact of the MOTIVES intervention for these two groups. Logit estimation will be used for binary outcome measures.

We will impute missing data for some variables if an individual is still enrolled. When participants drop out, we will fit multiple logistic regression models to assess whether this dropout is random. If it is not, we will construct “non-response” weights using logistic regression that correct for dropout. Analyses will reflect these design effects in the calculation of standard errors and tests of significance.

In summary, the primary purposes of our pilot study are to demonstrate the acceptability and feasibility of methods proposed for a subsequent large-scale trial, to stabilize procedures so they are replicable, and to determine important parameters with sufficient accuracy to allow reliable estimates of sample size, power, and detectable effects for the subsequent study. “Mission-critical” parameters include proportions for dichotomous endpoints (such as agreeing to be enrolled in the trial, positive result by HIV rapid test); means and standard deviations for continuous endpoints (such as frequency of repeat HIV-negative test result); and the spectrum of response profiles for longitudinal studies (such as improvement or degradation in retention of HIV prevention information).

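### Knowledge ANCOVA covariates are chosen by chance baseline imbalance, so the enrolment HIV-KQ-18 score usually stays out and the precision the rule aims for is mostly not obtained

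*Protocol article*

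**What the plan says.** In the Data analysis section, group differences are to be tested by ANCOVA, "controlling for relevant client characteristics that are found to differentiate the groups at baseline in order to improve the precision" over a simple ANOVA. No test or threshold for judging a difference is given. The regression model is justified in the same way: "In small samples efficiency can be improved by controlling for differences in control variables between the groups that may arise due to chance". That section adds that the regression "can be implemented in differences rather than levels", gives a formula for the difference in mean change, and plans repeated-measures models.

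The section also states that "the primary outcomes include HIV knowledge and frequency of HIV testing". Table 1 (Measures: health outcomes) lists HIV knowledge, measured by the HIV-KQ-18, at "enrollment, 6 & 12 months". Testing behaviour is listed as "Extracted from *Bienestar* clinic data", with no time point visible in the extracted table. Neither appears among the table's covariates of interest, and no fixed adjustment set is named.

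Two phrases in the section do not match the listed outcomes. The mean comparison is described as one "of the group means in adherence levels", and the longitudinal analysis is said to "examine whether self-reported sexual behaviors persist or decline similarly between the two groups".

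**The concern.** The rule and its stated reason do not fit together. In a randomised comparison, adjustment reduces the variance of the treatment effect to the extent that the covariate is correlated with the outcome. Whether that covariate differs between arms in the realised sample is a matter of chance and says nothing about its prognostic value. The covariate most likely to be prognostic for follow-up knowledge is the same score at enrolment. It is measured in everyone before randomisation, yet the rule admits it only when the arms happen to differ on it. The rule also makes the model depend on the data, so the form of the knowledge estimate is unknown until the baseline table has been examined.

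At stake is the width of the interval for the knowledge effect. The abstract says the pilot will also supply point and interval estimates to inform a fully powered study.

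**Working it through.** **Inputs from the protocol article.** About 90 MSM and 10 TGW per arm (Design), so 100 per arm and 200 in total; 1:1 allocation; HIV-KQ-18 at enrolment, 6 and 12 months. The article states no alpha, power, effect size, SD or correlation, so there is no power figure to reproduce.

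**Assumptions, not in the article.** Two-sided alpha 0.05; true effect 0.4 SD; correlation r between enrolment and follow-up score of 0.3, 0.5 or 0.7; a covariate counts as differing when its baseline p-value is below 0.05 or 0.20; no dropout; a continuous, normal outcome.

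**Step 1: what each analysis can achieve.** In SD units, the standard error from follow-up means alone is √(2/100) = 0.141. Relative to that variance, always adjusting for the enrolment score gives 1 − r², and the change score gives 2(1 − r). Power is Φ(0.4/SE − 1.96). For example, at r = 0.5 the adjusted SE is 0.1414 × √0.75 = 0.1225, and Φ(3.266 − 1.960) = 90.4%.

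| r | Variance ratio, always adjusted | Variance ratio, change score | Power, follow-up means | Power, always adjusted | Power, change score |
|---|---|---|---|---|---|
| 0.3 | 0.91 | 1.40 | 80.7% | 84.3% | 66.7% |
| 0.5 | 0.75 | 1.00 | 80.7% | 90.4% | 80.7% |
| 0.7 | 0.51 | 0.60 | 80.7% | 97.7% | 95.5% |

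Always adjusting makes 200 participants worth 200/0.91 = 220, 200/0.75 = 267 and 200/0.51 = 392 unadjusted participants.

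**Step 2: what the stated rule achieves.** Each simulated trial tested the enrolment score for imbalance and adjusted for it only if the test was positive. By construction, the score was selected in about 5% of trials at the 0.05 threshold and 20% at 0.20. Results from 60,000 trials per setting:

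| r | Threshold | Power, rule | Power, always adjusted | Type I error, rule |
|---|---|---|---|---|
| 0.3 | 0.05 | 81% | 84% | 4.8% |
| 0.5 | 0.05 | 81% | 90% | 4.3% |
| 0.7 | 0.05 | 82% | 98% | 3.6% |
| 0.3 | 0.20 | 81% | 84% | 4.5% |
| 0.5 | 0.20 | 84% | 90% | 3.7% |
| 0.7 | 0.20 | 87% | 98% | 2.6% |

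Separate runs of 5,000 and 10,000 trials agree to within about one percentage point of power (81–82% for the rule at r = 0.5, threshold 0.05).

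**Step 3: the reported interval.** At r = 0.5 and threshold 0.05, the mean 95% interval width was 0.557 unadjusted, 0.554 under the rule and 0.484 always adjusted. The rule narrows it by 0.003/0.557, under 1%; prespecified adjustment narrows it by 0.073/0.557 = 13%. At a 0.20 threshold the average width is at best 0.8 × 0.557 + 0.2 × 0.484 = 0.542, a narrowing of about 3%.

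**Step 4: why the test is conservative.** At r = 0.5 and threshold 0.05, the SD of the estimate across trials is 0.141 unadjusted, 0.136 under the rule and 0.123 always adjusted. The rule corrects the trials with the largest imbalance, so estimates vary somewhat less. In the roughly 95% of trials where nothing is selected, the unadjusted standard error is still reported and is slightly too large for the procedure as a whole. At 0.20 the SD falls further, to 0.130, but the reported intervals do not show that gain.

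**The case against.** The strongest reply is that enrolment knowledge is not discarded. The change comparison, the regression in differences and the repeated-measures models can all use it, and at r = 0.7 the change score has 95.5% power against 97.7% for adjustment. This stands as a limit on the point: a reader might infer that baseline knowledge goes unused throughout, and the article does not support that. It does not rescue the ANCOVA rule. The change score is no better than follow-up means at r = 0.5 and is worse below it.

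The size also depends on a correlation and a threshold that the article does not give. At r = 0.3 only about three points of power are at issue.

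Other stronger readings fail:

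- **Inflated false positives.** The simulated error rate lies below 5%.
- **The same loss for testing.** Nothing was computed for that outcome. The binary version is planned as logistic regression, to which linear variance ratios do not carry over.
- **An earlier testing count already in hand.** Table 1 names clinic data as the source, but nowhere does the article say that an individual pre-enrolment count is abstracted, and eligibility requires no earlier visit.
- **A compromised pilot.** Data analysis puts acceptance and feasibility first, and the covariate rule leaves simple proportions, means and SDs untouched.
- **Formulas tied to unlisted outcomes.** E[Y] is defined generically and the same section names the dependent variables, so the stray phrases are an editorial matter.

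**Conclusion.** The point holds in this limited form. The selection rule is stated in the article, so it is not a detail left to an unseen analysis plan, and it does not serve the precision it is meant to deliver. For the HIV-knowledge ANCOVA and level regression, the enrolment score would be left out in about 80% to 95% of trials at conventional thresholds. At the 0.05 threshold the cost is roughly 3 percentage points of power at r = 0.3, 8 to 9 at r = 0.5 and 15 to 16 at r = 0.7, with a test that is mildly conservative (type I error about 4%). These figures rest on the assumed 0.4 SD effect, two-sided 5% level, 100 per arm and no dropout. The direction does not depend on the exact values, provided that the enrolment score predicts follow-up knowledge. The consequence is wider intervals for an effect estimate that ranks below the feasibility aims.

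**What to change.** In Data analysis, delete the selection of covariates by baseline difference, in both the ANCOVA sentence and the justification of the regression model. State instead that every HIV-knowledge ANCOVA or regression includes the enrolment HIV-KQ-18 score as a covariate, whatever imbalance is observed.

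For the testing models, first establish whether clinic records give pre-enrolment testing frequency for all participants. If they do, prespecify it in the same way; if not, leave it out.

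As an editorial correction, name Y as the HIV-KQ-18 score and as HIV testing frequency, in place of the references to adherence and to self-reported sexual behaviour.

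For HIV knowledge this changes wording only, because the score is already collected before randomisation. For testing, the cost is a check of the clinic records and, if they suffice, possibly some extra abstraction. The change should be made before outcome data are compared by arm.

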### Design

We will pilot test the feasibility and acceptability of the intervention in a small RCT among 200 Latino/a MSM and TGW from Bienestar Human Services, Inc.’s (*Bienestar*) HIV testing sites. There will be approximately 90 MSM and 10 TGW in each arm. Participants will complete a survey at baseline, six, and 12 months. Participants will be randomized (procedures for this are described in detail below) into either the “information only” group (e.g. receiving text messages with HIV prevention information) or the “information plus” group (e.g. additionally receiving quiz questions that provide the possibility of winning prizes when answered correctly). Randomization will provide the comparison needed to identify the potential effect of winning a prize.

We will pilot the recruitment process with five participants. We will begin with a staggered enrollment process based on previous HIV testing data to identify the highest volume *Bienestar* sites. During the study we are collecting quantitative data on both primary outcomes (e.g. HIV knowledge and frequency of testing behavior) and secondary outcomes (e.g. HIV status).

All participating institutions received approval from their respective Institutional Review Boards and a certificate of confidentiality has been obtained from the National Institute of Mental Health. Any protocol modifications will be submitted to the IRBs for review, and participants will be informed if warranted. The trial was registered on 5 May 2017 with the ClinicalTrials.gov registry (NCT03144336).

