### MOTIVES intervention

Figure 1 details all stages of the MOTIVES intervention. Participants will be recruited by each tester after they complete their HIV test and the tester assesses that they may be eligible. Other HIV testers who are not part of MOTIVES are aware of the study and will be given flyers with the study information to provide to clients who might be eligible or interested. Eligible clients who express interest will participate in the consent process. Clients will receive a brief overview of the study and a description of the HIV prevention information and prize drawing components. The consent process will also make it clear that only half of the participants will be randomly assigned to the prize drawing group, but that all participants will receive the weekly information messages. Participants will also receive an additional consent document asking them to save the study phone number as “MOTIVES.” If they do not have a lock code on their phone, we will ask if they would like help in creating a code to increase privacy. The study team will confirm that the participants know how to delete messages if they have concerns about someone else reading their messages. The MOTIVES testers will give them information about when to expect text messages from the study (e.g. 2 pm on Thursday every week for one year and a reminder every 2.5 months to test again). The targeted testing frequency is at least once every three months. We will give participants examples of the kinds of text messages and quizzes they will receive and we will explain the odds of winning if they are in the intervention group. The hard copy of the signed consent form will be stored in a locked cabinet at each recruitment site. Following the consent process, the participant will be enrolled in the study by completing the Study Contact form that requires them to provide three tracking mechanisms and assigns them a Study ID number.

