At enrollment, we will take several steps to ensure the confidentiality of participants related to text message communication. For example, as mentioned above, MOTIVES HIV testers will instruct participants how to properly use the SMS system, maintain privacy on their device, and delete SMS messages from their mobile device. Finally, study staff will call the participant (either using an office line or using the *67 feature to make a protected call using their personal cell phone) to confirm that study staff has the correct cell phone contact number for the participant. At this time, participants will receive a $15 gift card.

After participating in the baseline survey and receiving their gift card, participants will be randomized using computer allocation by the study PI. The goal is to ensure that the randomization process does not influence responses to the baseline survey (e.g. responding more quickly if they were not chosen for the prize drawing group and feeling disappointed and less invested in the study). The study design was guided by its purpose as a pilot trial; we used a 1:1 randomization as it provides the greatest power for testing effectiveness in preparation for a future definitive RCT. Hereafter we will refer to the two groups as: (1) Information plus group (intervention group); and (2) Information only group (control group). HIV testers will also reaffirm that assignment is completely random and not based on the personal characteristics of any individual client. RAND study staff will explain to testers why randomization is so important, underscoring that only with their help can we actually understand if the intervention works. If testers select participants based on their own judgment of who is most in need of the intervention (e.g. they think a client appears particularly poor and would really appreciate having gift cards), we would not be able to collect accurate data. If a certain type of client is consistently included in the information plus reminders group, we will not be able to determine if the intervention works with everyone or just with a particular type of person.

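### McNemar's test, a paired-data test, is assigned to a comparison of two unpaired randomised arms; the error is confined to the unadjusted test of binary outcomes

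*Protocol article*

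**What the plan says.** The Data analysis section of the protocol article sets the rule for binary outcomes, with testing in a three-month window as its example: "we will use a non-parametric McNemar’s test and an analogous multiple logistic regression to control for covariates to assess group differences". The purpose given is a comparison of groups. The sentence before it gives ANCOVA the same purpose, and the next paragraph defines impact as D, the expected outcome in the intervention arm minus that in the control arm, in levels or in changes. Later the section adds: "Logit estimation will be used for binary outcome measures".

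The design is unpaired. The Design section has "Participants will be randomized (procedures for this are described in detail below) into either the “information only” group" or the information-plus group, with about 100 people per arm. Under MOTIVES intervention, "participants will be randomized using computer allocation by the study PI", at a ratio of 1:1. Neither section mentions matching, and nothing limits McNemar's test to change within a person or defines a pair.

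HIV testing is one of the two primary health outcomes in Table 1.

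**The concern.** McNemar's test compares the two kinds of discordant pair in a set of paired yes/no observations. Two independently randomised arms supply no such pairs, so the named test does not match the contrast D that the same section defines. An analyst following the text must either pair each person with themselves over time, which answers a different question, or invent pairs across the arms.

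At stake is the unadjusted result for the binary form of a primary health outcome. The abstract promises point and confidence interval estimates to inform a later powered trial. A p-value for change over time, read as an intervention effect, could be carried into that trial's planning.

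**Working it through.** The document gives no testing rate, effect size, alpha or power for HIV testing, so there is no stated figure to reproduce. The one available sum agrees: 2 × (90 + 10) = 200.

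**What the statistic contains.** With b and c the two discordant counts, McNemar's statistic is (b − c)²/(b + c). If the pair is one person at baseline and follow-up, b and c count changes in each direction. The arm does not enter, so the statistic cannot reflect D.

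**Within-person pairs, simulated.** From the document: 100 per arm, two unpaired arms. Assumed: the testing rates, a latent within-person correlation of 0.3, two-sided 5% level; 4,000 simulated trials per row. Entries are the percentage of trials rejecting.

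| Baseline; follow-up intervention / control | McNemar, arms pooled | McNemar, intervention arm only | Two-sample test | McNemar, arbitrary cross-arm pairs |
|---|---|---|---|---|
| 30%; 30% / 30% | 5.3 | 5.2 | 4.8 | 4.5 |
| 30%; 45% / 45% | 93.3 | 67.3 | 5.4 | 4.8 |
| 50%; 60% / 40% | 4.8 | 35.0 | 83.1 | 81.2 |

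In the second row there is no arm effect, yet the within-person test nearly always rejects because both arms moved. In the third row there is a 20-point arm difference, but the changes of +10 and −10 points cancel, so the pooled test rejects at only its nominal rate. As an analytic check on the two-sample test, power for 60% against 40% with 100 per arm is 81%.

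**Arbitrary cross-arm pairs.** Take 60/100 against 46/100 as an illustration.

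- Two-sample test: pooled proportion 106/200 = 0.53; SE = √(0.53 × 0.47 × 2/100) = 0.0706; z = 0.14/0.0706 = 1.98; p = 0.047.
- McNemar: b − c = 60 − 46 = 14 however people are paired, so the statistic is 196/(b + c). Only the number of discordant pairs varies, and the pairing sets it.
- Over 5,000 random pairings p ran from 0.020 (196/36 = 5.44) to 0.090 (196/68 = 2.88), and 51% of pairings gave p below 0.05.

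The data are the same throughout; only the invented pairing changes.

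**The regression.** Logistic regression on arm and covariates, one record per person for a given period, estimates the arm effect as an odds ratio and needs no pairing. It is not the regression counterpart of McNemar's test, which is conditional logistic regression on the pairs, so calling it *analogous* is inaccurate.

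**The case against.** The strongest reply is that the plan already contains a sound analysis. The same sentence names logistic regression for group differences, the section repeats that logit estimation applies to binary outcomes, and it calls the simple comparison D the most direct evaluation. The section also puts acceptance and feasibility first, and no decision rule depends on McNemar's test. All of this stands and limits the harm. It does not rescue the named test. Nor is this detail left to an analysis plan, because the article names a specific test for a specific purpose.

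A reader might infer more, in three ways that the documents do not support:

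- **That no arm comparison is possible.** Arbitrary cross-arm pairing kept its level (about 5%) and similar power (81% against 83%). The fault there is a p-value that cannot be reproduced, not an impossible test.
- **That everyone counts as tested at baseline**, because "Participants will be recruited by each tester after they complete their HIV test", so that each arm must show a significant decline. No section makes the enrolment test the baseline value of the indicator; pairs could use a pre-enrolment period or two follow-up periods. Even on that reading the exact p-value is 2 × 0.5^b, with b the number not tested later. It is 0.0625 at b = 5, so an arm of 100 with 95 or more tested would not show a significant decline.
- **That the logistic regression has an inflated error rate.** Four periods in one unclustered model, with an assumed correlation of 0.2 to 0.5, would have a design effect of 1 + 3 × 0.2 = 1.6 to 1 + 3 × 0.5 = 2.5, and a nominal 5% error of about 12% to 22%. The article never proposes that model; it speaks of comparisons at each time point and of repeated-measures methods.

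**Conclusion.** The rule is wrong as written: a paired test is assigned to an unpaired comparison on a primary health outcome. That conclusion rests on the text alone. The rejection rates depend on assumed testing rates and correlation, and serve only to show that the within-person test can err in both directions.

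The error is confined to the unadjusted test. The logistic regression remains valid for the arm contrast when one period is analysed at a time, so it would be wrong to infer that the trial lacks a usable binary analysis. Given that, and the pilot's feasibility and acceptability aims, severity is moderate.

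**What to change.** In the Data analysis section:

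- Replace McNemar's test with a two-sample comparison of proportions for each three-month period: risk difference with 95% CI, and a chi-square or Fisher exact test. The article already uses chi-square for another unpaired comparison, participants against non-participants.
- Keep the logistic regression as the covariate-adjusted version and drop the word that calls it analogous to McNemar's test.
- State that if several periods are analysed together, within-person correlation will be accounted for, for example by GEE logistic regression or standard errors clustered on participant.
- If McNemar's test is kept, label it as describing within-arm change only, and define the two time points that form a pair.

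The cost is a change of analysis wording. Sample size, data collection and trial conduct are unaffected.
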